# The effect of changing stool collection processes on compliance in nationwide organized screening using a fecal occult blood test (FOBT) in Korea: study protocol for a randomized controlled trial

**DOI:** 10.1186/1745-6215-15-461

**Published:** 2014-11-26

**Keywords:** Colorectal cancer, Colorectal neoplasm, Early detection of cancer, Fecal occult blood test, Randomized control trial, Factorial design

## Abstract

**Background:**

Colorectal cancer (CRC) screening by fecal occult blood test (FOBT) significantly reduces CRC mortality, and compliance rates directly influence the efficacy of this screening method. The aim of this study is to investigate whether stool collection strategies affect compliance with the FOBT.

**Methods/Design:**

In total, 3,596 study participants aged between 50 and 74 years will be recruited. The study will be conducted using a randomized controlled trial, with a 2 × 2 factorial design resulting in four groups. The first factor is the method of stool-collection device distribution (mailing vs. visiting the clinic) and the second is the type of stool-collection device (sampling kit vs. conventional container). Participants will be randomly assigned to one of four groups: (1) sampling kit received by mail; (2) conventional container received by mail; (3) sampling kit received at the clinic; (4) conventional container received at the clinic (control group). The primary outcome will be the FOBT compliance rate; satisfaction and intention to be rescreened in the next screening round will also be evaluated. The rates of positive FOBT results and detection of advanced adenomas or cancers through colonoscopies will also be compared between the two collection containers.

**Discussion:**

Identifying a method of FOBT that yields high compliance rates will be a key determinant of the success of CRC screening. The findings of this study will provide reliable information for health policy makers to develop evidence-based strategies for a high compliance rate.

**Trial registration:**

CRIS:KCT0000803

Date of registration in primary registry: 9 January, 2013.

**Electronic supplementary material:**

The online version of this article (doi:10.1186/1745-6215-15-461) contains supplementary material, which is available to authorized users.

## Background

Colorectal cancer (CRC) is a major health care concern worldwide, with a high incidence and mortality rate. About 1.23 million new cases of CRC and 608,000 associated deaths were estimated worldwide in 2008[1]. In developed western countries, CRC mortality and incidence are decreasing, while the incidence remains high in Asian countries such as Japan, China, South Korea, and Singapore[2, 3]. In Korea, CRC caused 25,782 new cases (35.9 per 100,000) and 7,645 (10.4 per 100,000) deaths in 2010[4].

Based on reports that CRC screening by a fecal occult blood test (FOBT) significantly reduces CRC mortality[5–8], several countries have implemented FOBT screening at the national or regional level[9]. In England, the National Health Service Bowel Cancer Screening Program (NHSBCSP) adopted a biennial guaiac-based FOBT for those aged 60 to 75[10]. In Korea, the National Cancer Screening Program (NCSP) offers annual fecal immunochemical testing (FIT) to people aged 50 years or older[11].

Although a FOBT is relatively simple, inexpensive, and noninvasive compared to colonoscopy, the rate of FOBT screening varies from 20% to 71% among countries[9]. In Korea in 2012, the rate of FOBT screening was only 25.7%[12]. Several barriers, including health system, provider, and patient factors, contribute to the low rate of FOBT screening[13–16]. In Korea, the system-related barriers to an efficient screening process have been reported to be the requirement for two consecutive clinic visits to receive the stool device and submit the sample, and the use of a stool container that has a short, thick sampling probe to collect stool samples[17]. To overcome these barriers, two interventions are being considered. The first is to distribute stool-collection devices by mail, which requires only one clinic visit to submit the sample. The second is to provide a stool sampling kit consisting of a small test tube including a longer, thinner sampling probe that is easier to poke into the stool to collect stool specimens. Through these interventions, this study will determine the most effective strategy to increase compliance and satisfaction in FOBT screening. This determination is based on the assumption that changing the stool-collection process (especially as regards the type of stool-collection device) will not affect the results of FOBTs, but may affect compliance and satisfaction. We will therefore compare the rates of positive FOBT results between the two stool devices to validate our assumptions.

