**Illustrations of stool devices: (a) conventional container; (b) sampling kit.**

### Outcome measures

The primary outcome will be compliance with FOBT screening; compliance will be defined as the proportion of individual participants who submit stool specimens to the National Cancer Center within two weeks following receipt of collection devices. The secondary outcome will be participant satisfaction and intention to be rescreened in the next screening round as assessed by questionnaire at the clinic. The questionnaire will use a five-point Likert scale (1 = strongly disagree, 2 = disagree, 3 = uncertain, 4 = agree, 5 = strongly agree) with three dimensions: satisfaction with each process, from receiving stool devices to submission of specimens at the clinic; overall satisfaction with the entire process; and intention to be rescreened. The tertiary outcome will be the rates of positive FOBT results using sampling kits vs. conventional containers. Positive results are defined as those exceeding 100 ng/mL blood. All participants who undergo FOBT will be informed of the screening results via mail within three weeks, and those whose results are positive will be recommended to undergo colonoscopy. Colonoscopy or further biopsy for abnormal lesions will be performed by highly qualified colonoscopists upon provision of written consent at the NCC. Histopathological results will allow comparison of the detection rates of advanced adenoma or cancer between sampling kits and conventional containers. All outcomes of the study will be explained to respondents upon interview and prior to obtaining written informed consent.

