### Statistical analysis

Compliance rates for FOBT screening will be compared among the four groups by a chi-square test. The satisfaction and intent to rescreen using a FOBT will be assessed by analysis of variance (ANOVA). The rates of positive FOBTs and the rates of advanced adenoma or cancer detected by colonoscopy using the different stool devices will also be analyzed by a chi-square test. The adjusted odds ratios (ORs) and 95% confidence intervals (CIs) of each outcome will be calculated using multiple logistic regression. All data will be analyzed using the SAS software, version 9.2 (SAS Institute, Inc., Cary, NC, USA).

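### The assumption that the device does not alter FOBT results is to be validated by a test of difference with no margin or decision rule, so a non-significant result could be misread as validation

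*Protocol article*

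**What the plan says.** The Background states the premise that "changing the stool-collection process (especially as regards the type of stool-collection device) will not affect the results of FOBTs", though compliance and satisfaction may change. It then gives the purpose of the device comparison: "We will therefore compare the rates of positive FOBT results between the two stool devices to validate our assumptions".

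Outcome measures makes this a named outcome: "The tertiary outcome will be the rates of positive FOBT results using sampling kits vs. conventional containers". The cut-off is fixed ("Positive results are defined as those exceeding 100 ng/mL blood"), but no expected positivity rate is given.

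Statistical analysis sets the method. For the lesion outcome, "the rates of advanced adenoma or cancer detected by colonoscopy using the different stool devices will also be analyzed by a chi-square test"; the same sentence applies the chi-square test to positivity. It adds: "The adjusted odds ratios (ORs) and 95% confidence intervals (CIs) of each outcome will be calculated using multiple logistic regression". No equivalence hypothesis, margin or rule of interpretation accompanies either analysis. The only sample size calculation in the article is for compliance, mail against clinic.

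**The concern.** The statement to be supported is that the device makes no difference. The null hypothesis of a chi-square test is that same statement. Rejection would count against the premise, but failure to reject leaves it where it was, and the less information there is, the easier it is not to reject. The stated method therefore cannot deliver the stated aim.

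The premise also needs checking on the article's own facts. According to Interventions, the kit takes roughly 10 mg of stool on a grooved probe, whereas specimens in the conventional container are moved into kits in the laboratory before analysis. Sampling and handling thus differ by device, and the result is judged against a fixed quantitative cut-off. If the kit raised compliance but also shifted positivity, a recommendation of the kit would rest on a premise that the trial had not established.

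Only participants who submit a specimen have a result, so the comparison uses about a third of those randomised. Lesions found at colonoscopy are a small fraction of those again, yet an adjusted logistic model is planned for every outcome.

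**Working it through.** **The plan's own sample size.** The stated formula (two-sided 5%, 80% power, equal groups) gives 1,398 per group for 36% against 31%, and 1,438 with continuity correction. Then 1,438 / 0.8 = 1,797.5, rounded up to 1,798, and 2 x 1,798 = 3,596. The article quotes 30.8% for the clinic rate; unrounded, that would give 1,291 and 1,329. This calculation concerns compliance only and is used here just for the number enrolled.

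**Specimens per device.** Allocation is 1:1:1:1, so each device has 1,798 participants, half by mail and half at the clinic. Mean planned compliance is (30.8% + 36%) / 2 = 33.4%.
- As enrolled: 1,798 x 0.334 = about 600 (554 at 30.8%, 647 at 36%).
- After 20% loss: 1,438 x 0.334 = about 480.

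**Power of the test of difference.** Positivity is an assumption, shown at 3%, 5% and 10%. Power = Φ((|p1 − p2| − 1.96·SE0) / SE1), where SE0 = √(2p̄(1 − p̄)/n) and SE1 = √((p1(1 − p1) + p2(1 − p2))/n).

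Example, 5% against 7.5% with n = 600: SE0 = √(2 x 0.0625 x 0.9375 / 600) = 0.01398; SE1 = √((0.0475 + 0.069375) / 600) = 0.01396; (0.025 − 0.02739) / 0.01396 = −0.171; power = 43%.

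**Precision.** The 95% half-width for a difference is 1.96·√(2p(1 − p)/n). At 5% and n = 600: 1.96 x 0.01258 = 2.5 points.

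| Assumed positivity | Power for 1.5-fold, n = 600 | Power for 1.5-fold, n = 480 | 95% CI half-width, n = 600 |
|---|---|---|---|
| 3% | 28% | 23% | 1.9 points |
| 5% | 43% | 36% | 2.5 points |
| 10% | 75% | 65% | 3.4 points |

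For 5% against 7%, power is 31% (n = 600). For a doubling from 5% to 10% it is 91%.

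**Equivalence by two one-sided tests** (5% each, true difference zero). Power = 2Φ(margin/SE − 1.645) − 1, floored at 0, with SE = √(2p(1 − p)/n). At 5% and n = 600, SE = 0.01258.
- 2-point margin: 0.02 / 0.01258 = 1.59, below 1.645, so power is about 0%.
- 3-point margin: 0.03 / 0.01258 − 1.645 = 0.74, so power is 2 x 0.770 − 1 = 54%.

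Over the assumed range with n = 600, a 2-point margin gives 30% at 3% positivity and about 0% at 10%; a 3-point margin gives 84% and 7%. At 3% positivity, however, a 3-point margin is as wide as the rate itself.

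For 80% power the number tested per device is 2p(1 − p)(1.645 + 1.282)² / margin². At 5% positivity that is 2,034 for 2 points and 904 for 3 points.

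**Lesions.** At 5% positivity, 600 x 0.05 = 30 positives per device. With an assumed 20–30% yield of advanced adenoma or cancer, that is 6 to 9 per device, or 12 to 18 in all, assuming every positive has a colonoscopy. Across 3% to 10% positivity the count runs from 600 x 0.03 x 0.20 = 3.6 to 600 x 0.10 x 0.30 = 18 per device.

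**The case against.** Several points on the other side have force.

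- **Interpretation.** A reader might infer that the trial will take non-significance as proof of no effect. No sentence says so. The risk comes from the stated aim of validation combined with a difference test and no rule; it is a possible misreading, not a declared one. This stands.
- **Intervals are planned.** Adjusted odds ratios with 95% CIs would show how large a device effect remains compatible with the data. This deserves credit. A margin is also the kind of detail an unseen analysis plan may hold, so its absence alone would be no finding. But the article itself states both the aim and the method, and the two do not match.
- **Size of the risk.** A reader might infer that any material shift would most likely be missed. That holds for a 1.5-fold change at about 5% positivity or below, but not at 10% (75% power), nor for a doubling at 5% (91%).
- **Number tested.** Study integrity says that only people who submit a sample are included, which sits badly with the sample size section. If all 1,798 per device had results, power for 5% against 7.5% would be 87%, and equivalence within 2 points at 5% positivity would have 73% power. The one-third reading fits the compliance outcome better, and the test would still address the wrong hypothesis.
- **Lesions.** A reader might conclude that counts are too low for a valid chi-square test. With 6 to 9 expected per device, the smallest expected cell exceeds the usual minimum of 5; it falls below only at the low end of two assumed rates. Invalidity is not shown. Very low power and the adjusted model remain fair criticisms. The Background proposes positivity, not lesions, for the validation, so this part is secondary.

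**Conclusion.** The concern holds in this form: the article sets out to validate an assumption of no device effect and specifies a test that can only refute it, with no margin or decision rule attached to the intervals it plans. A non-significant result could be misread as validation.

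How uninformative such a result would be depends on positivity, which the article does not give. With about 600 specimens per device, a 1.5-fold change is detected with 28% to 75% power over 3% to 10% positivity, and the difference is known to within about 2 to 3.5 points either way. These figures rest on the plan's compliance rates, on the device not itself changing compliance, and on the assumed positivity; 480 per device makes them worse. For advanced lesions, 12 to 18 events in total (under assumed positivity and yield, and fewer with incomplete colonoscopy uptake) give very low power and cannot support a multiple logistic model.

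The documents do not support saying that non-significance will be taken as proof, that a material shift would be missed at every plausible positivity, or that the chi-square test is invalid. The outcome is tertiary, but the Background makes the conclusion about strategy depend on it, so the point should be corrected before results are seen.

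**What to change.** For positivity, make the main device analysis an estimate of the kit-minus-container difference with its 95% CI. Fix an equivalence margin, with its justification, before results are seen. Claim that the device has no effect only if the 90% CI lies wholly inside the margin. Otherwise report that this is not established, and do not call the assumption validated.

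For advanced adenoma or cancer, give counts and rates by device with exact CIs, labelled descriptive, and drop the adjusted odds ratio for this outcome.

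The change is to analysis wording; it needs no new data and no change of design. The real cost is in what can be concluded. Equivalence is unlikely to be shown at this size unless positivity is low or the margin is wide: at 5% positivity and 600 per device, power is about 0% for a 2-point margin and 54% for a 3-point margin. The plan should say this in advance. If no defensible margin is within reach, the comparison should be presented as exploratory estimation only.

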## Methods

### Trial design

The study will be conducted using a 2 × 2 factorial randomized control trial (RCT) design resulting in four groups. The first factor is the two methods of distributing stool devices (mailing vs. visiting a clinic), and the other is the two stool devices (sampling kit vs. conventional container). Thus, the study will be composed of four groups from two factors (allocation ratio1:1:1:1): (1) sampling kit received by mail; (2) conventional container received by mail; (3) sampling kit received at the clinic; (4) conventional container received at the clinic (control group) (Figure 1).

**Figure 1 Fig1:**
[figure not shown]
**Flow chart of the study.**

### Participants

Individuals aged 50 to 74 years living in Goyang will be recruited from February 2013 to February 2015. The National Cancer Center (NCC) in Goyang has sufficient resources to screen all NCSP recipients living in the Goyang urban area. The study will take place at the NCC Center for Cancer Prevention and Detection. Invitation letters including a brief description of FOBT screening and the purpose of the study will be mailed to target participants, and those who want to participate in the study will provide verbal consent via telephone. After study staff confirms that they meet the study criteria, eligible participants will be randomly allocated to one of four groups. Written informed consent will be obtained from all participants upon visiting the clinic to submit stool specimens within two weeks after receiving a stool device. Exclusion criteria include: a prior diagnosis with any cancer including colorectal cancer; a history of colonoscopy or polypectomy; or a history of a FOBT more recent than one year. Ethical approval has been obtained from the Institutional Review Board at the NCC (NCCNCS-12-683).

### Interventions

There will be four groups: sampling kit received by mail, conventional container received by mail, sampling kit received at the clinic, and conventional container received at the clinic (control group). Sampling kits are being purchased from Eiken Chemical Co., Ltd., Tokyo, Japan. Compared to the currently used conventional container, the new sampling kit is thinner and smaller, with a thin (4.2 cm long) sampling probe attached to the cap that allows easier insertion into the stool. The tip of the sampling probe has a spiral groove to collect stool specimens (Figure 2). The sampling probe with the collected stool (approximately 10 mg) may then be reinserted into the kit. These stool specimens are analyzed in an OC-SENSOR DIANA machine (Eiken Chemical Co., Ltd., Tokyo, Japan) designed for quantitative immunochemical FOBTs and the sampling kits fit this equipment. Stool specimens in conventional containers are transferred to sampling kits for immunochemical FOBTs at the laboratory because the conventional containers do not fit the analyzer. Mailed sampling kits or conventional containers will include an instruction leaflet. All participants who receive stool devices will be instructed in methods of stool collection via telephone or face-to-face by research staff.

**Figure 2 Fig2:**
[figure not shown]
**Illustrations of stool devices: (a) conventional container; (b) sampling kit.**

### Outcome measures

The primary outcome will be compliance with FOBT screening; compliance will be defined as the proportion of individual participants who submit stool specimens to the National Cancer Center within two weeks following receipt of collection devices. The secondary outcome will be participant satisfaction and intention to be rescreened in the next screening round as assessed by questionnaire at the clinic. The questionnaire will use a five-point Likert scale (1 = strongly disagree, 2 = disagree, 3 = uncertain, 4 = agree, 5 = strongly agree) with three dimensions: satisfaction with each process, from receiving stool devices to submission of specimens at the clinic; overall satisfaction with the entire process; and intention to be rescreened. The tertiary outcome will be the rates of positive FOBT results using sampling kits vs. conventional containers. Positive results are defined as those exceeding 100 ng/mL blood. All participants who undergo FOBT will be informed of the screening results via mail within three weeks, and those whose results are positive will be recommended to undergo colonoscopy. Colonoscopy or further biopsy for abnormal lesions will be performed by highly qualified colonoscopists upon provision of written consent at the NCC. Histopathological results will allow comparison of the detection rates of advanced adenoma or cancer between sampling kits and conventional containers. All outcomes of the study will be explained to respondents upon interview and prior to obtaining written informed consent.

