### Sample size calculation

Study participants will be divided into two groups according to the method of receiving the stool-collection device. To determine the sample sizes of two groups, we will establish the null hypothesis (H_0_) and alternative hypothesis (H_1_) using the difference *p*_*1*_*-p*_*2*_, where *p*_*1*_ is the expected compliance rate in the group receiving collection devices by mail and *p*_*2*_ is the expected compliance rate in those receiving them at a clinic.$$\begin{array}{l} H_{0}:p_{1}=\;p_{2}\left(\delta =p_{1}-\;p_{2}=0\right)\;\text{vs}.\\ H_{1}:p_{1}>p_{2}\left(\delta =p_{1}-\;p_{2}>0\right) \end{array}$$

The expected compliance rate of participants visiting a clinic is based on that observed in 2010 by the NCSP, which was 30.8%, and the compliance rate of participants receiving stool devices by mail is estimated at 36% based on the assumption that the rate will be at least 5% greater.$$N=\frac{{\left\{Z_{\frac{\alpha }{2}}\sqrt{\left(r+1\right)\bar{p}\left(1-\bar{p}\right)}+Z_{\beta }\sqrt{rp_{1}\left(1-p_{1}\right)+p_{2}\left(1-p_{2}\right)}\right\}}^{2}}{r{\left(p_{1}-p_{2}\right)}^{2}}$$

Based on the above formula, 1,398 people will be needed in each group to detect the difference *p*_*1*_*-p*_*2*_ in the proportions using a two-tailed test and 80% power (1-β) at a 5% significance level. However, continuity correction tests will be needed to estimate very closely approximate values, and thereby a sample size of 1,438 in each group will be required. Finally, to allow for a 20% loss to follow-up, we will enroll an additional 350 participants per group, resulting in a final total for each group of 1,798 participants; thus, a total of 3,596 participants will be enrolled in the study.

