### Randomization

After providing verbal consent by telephone, those who are eligible will be allocated to one of four groups by a computer-generated randomization program using the SAS 9.2 statistical software (SAS Institute, Inc., Cary, NC, USA). The sequence will be generated by simple randomization. Participants will be subjected to different trial conditions depending on the number they are allocated.

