### Study integrity

This study will use a randomized study design to evaluate whether distribution using mail delivery and an improved stool-collection device increase FOBT screening compliance. Participants will be recruited through letters of invitation and randomly assigned to one of four groups (three interventions and one control group). Participants will be included only if they submit a stool sample to the NCC in person within two weeks after receiving a stool device, and these participants will be rewarded with small gifts. To maintain consistency in data collection, we will assign two well-trained research staff members to oversee data management, supervise all steps, and train assistant staff throughout the study duration.

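### The two-week compliance window starts at device receipt, which in the clinic groups follows an untimed pick-up visit after randomisation, and the denominator does not settle how people who never collect a device are counted

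*Protocol article*

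**What the plan says.** Outcome measures in the Protocol article gives the measure as follows: "compliance will be defined as the proportion of individual participants". The people who count towards it are then described as those "who submit stool specimens to the National Cancer Center within two weeks following receipt of collection devices". The window is tied to receipt. The denominator is given only as individual participants.

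Background names the barrier under test as "the requirement for two consecutive clinic visits to receive the stool device and submit the sample". The first intervention is to "distribute stool-collection devices by mail, which requires only one clinic visit to submit the sample". Mailing thus removes the pick-up visit.

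Randomization fixes the order of events: "After providing verbal consent by telephone, those who are eligible will be allocated to one of four groups". Pick-up in the clinic groups therefore comes after allocation and before the two-week window opens. No section states a time limit for it.

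Two other sections bear on who is counted:

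- Sample size calculation words the clinic rate p2 as the expected compliance of those who get their devices at a clinic. Its planning value "is based on that observed in 2010 by the NCSP, which was 30.8" per cent. The section does not say whether that rate is per person invited or per device handed out.
- Study integrity says: "Participants will be included only if they submit a stool sample to the NCC in person within two weeks after receiving a stool device".

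**The concern.** The mailing factor acts on one step, getting the device into the participant's hands. The outcome window opens only once that step is complete. This has two consequences.

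The first is timing. A clinic-group participant may take any length of time to collect and still has two full weeks afterwards. A mail-group participant has two weeks from a delivery date that he or she does not choose. Total time from randomisation to a qualifying specimen is open-ended in one arm of the comparison and limited by the post in the other.

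The second is selection. A clinic-group participant who never collects has no receipt date. If such people leave the denominator, the clinic groups shrink to people who have already made one visit, while the mail groups keep nearly everyone randomised. Collectors are likely to be the more motivated, so a bias of this kind would run against mailing, in the comparison for which the trial is sized.

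**Working it through.** **Inputs.** From Sample size calculation: clinic rate 30.8%, mail rate 36%, two-sided 5% level, 80% power, 1,398 per distribution group without and 1,438 with continuity correction, 1,798 after 20% loss, 3,596 in total. Assumed, because the documents do not give it: f, the share of the clinic groups that collects a device, taken from 0.70 to 1.00. Also assumed: every mailed device counts as received.

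**The plan's own figure.** The printed formula with r = 1 and the pair 36% and 31% (30.8% rounded) gives

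{1.960·√(2 × 0.335 × 0.665) + 0.8416·√(0.36 × 0.64 + 0.31 × 0.69)}² / 0.05² = 1,398 after rounding up,

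and 1,438 with continuity correction. Then 1,438/0.8 = 1,797.5, rounded up to 1,798, and 2 × 1,798 = 3,596. The stated size reproduces with the rounded rate. The unrounded pair 36% and 30.8% gives 1,291 and 1,329. None of this depends on how non-collectors are counted, so the sample size does not answer the question.

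**Reading A: all randomised in the denominator.** A non-collector never submits and is non-compliant. The contrast is 36 − 30.8 = 5.2 points. With 1,438 per group:

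- power = Φ{(δ − 1.96·SE0)/SE1}, with SE0 from the pooled rate and SE1 from the separate rates
- = Φ{(0.052 − 1.96 × 0.01759)/0.01756} = 0.84.

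There is no selection bias. The uncounted pick-up delay remains. Its size cannot be calculated, because the document gives no pick-up times.

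**Reading B: only those who received a device.** If 30.8% and 36% are the rates among all randomised, the clinic rate becomes 30.8%/f on 1,438 × f people, and the mail rate stays at 36% on 1,438. The same power formula applies.

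| f (assumed) | Clinic rate per receipt | Mail minus clinic | Chance of a significant result for mail | Chance of a significant result for clinic |
|---|---|---|---|---|
| 1.00 | 30.8% | +5.2 points | 84% | 0% |
| 0.95 | 32.4% | +3.6 points | 51% | 0% |
| 0.90 | 34.2% | +1.8 points | 16% | 0.2% |
| 0.80 | 38.5% | −2.5 points | under 0.1% | 26% |
| 0.70 | 44.0% | −8.0 points | 0% | 98% |

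The break-even is f = 0.308/0.36 = 0.856, that is, about 14% of the clinic groups not collecting.

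**If the planning rates are instead per device received.** Then the clinic rate among all randomised is 30.8% × f. At f = 0.90 it is 27.7%, and the difference is 36 − 27.7 = 8.3 points, not 5.2. On either interpretation of the planning rates, the estimated effect depends on the denominator.

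**Which reading does the text support?** Outcome measures attaches the two weeks to the act of submitting and does not restrict the denominator to recipients. Participants uses that word for people at the moment of allocation. Both fit reading A. The wording of p2 and the inclusion sentence in Study integrity lean towards reading B or something narrower. No section states that all randomised people are analysed.

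**The case against.** A reader might infer that the primary outcome leaves out the barrier that mailing removes and is therefore biased against mailing. The document does not support that as a statement of fact. It requires a denominator limited to recipients, and Outcome measures does not state one. On the all-randomised reading a skipped pick-up visit lowers clinic compliance directly, so the barrier is largely captured. The sign reversal belongs to reading B alone.

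Two further points on that side stand:

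- The p2 wording can be no more than a label for the arm.
- The Study integrity sentence cannot define the denominator. Taken literally it would make compliance 100% in every group. It conflicts with the outcome definition and does not show a per-receipt analysis.

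It can also be argued that two weeks from receipt gives everyone the same time to use the device. That is true and is a reason to keep the measure as a description. It does not equalise the time from randomisation, which is what a comparison of distribution methods needs.

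Finally, a condensed article may leave analysis populations to a fuller document. Silence on the population would not be a finding by itself. Here, however, the article states the outcome rule. Its starting point comes after the step being tested, and two other sections pull its denominator in a different direction.

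**Conclusion.** The point holds in a limited form. Certain from the text: the window opens at receipt, receipt in the clinic groups follows an untimed visit after randomisation, and non-collectors have no start date. Delay before pick-up is thus uncounted and total time favours the clinic groups, by an amount the document does not allow one to calculate.

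Conditional: selection bias against mailing arises only if compliance is analysed per device received. Its size then rests on two further assumptions, that 30.8% and 36% are rates among all randomised and that f lies somewhere in the assumed range. Under them, 5% non-collection cuts power from 84% to 51%, and about 14% removes the effect. The present wording does not exclude that analysis, and the choice could change the main conclusion, so it should be settled before analysis.

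**What to change.** Define the primary outcome as the proportion of all randomised participants who submit a specimen within one fixed window counted from randomisation. The window should have the same length in all four groups and be long enough for postal delivery or pick-up. Choose its length without looking at outcomes by group. Count people who never collect a device as non-compliant. Keep submission within two weeks of receipt as a secondary description among recipients.

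Reconcile Outcome measures, Sample size calculation and Study integrity so that all three use this denominator, and state whether the 30.8% planning rate is per person invited or per device received.

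The cost is mainly wording, with three caveats. Stated compliance in the clinic groups may be lower. The change comes late: recruitment runs from February 2013 to February 2015 and the article is dated November 2014, about 21 months in, so the change must be dated, justified and made before the data are analysed. It also relies on randomisation and submission dates being recorded for everyone, which is likely but not stated.
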